## Abstract

**Background:**

Recent studies have demonstrated significant benefits associated with prehabilitation prior to major surgery. However, digital solutions in this domain are currently lacking. Our previous study, the Protego Maxima trial, reported positively assessed usability, validity, and safety of a prehabilitation application. In this randomized-controlled multicenter study, we aim to ascertain whether a digital prehabilitation program can reduce perioperative morbidity and costs in patients undergoing major surgery.

**Methods:**

The LUMOS trial is a multicenter prospective randomized-controlled trial comparing a 3-to-6-week interventional digital prehabilitation program with a digitized informational app, against a control group receiving only the informational application. The trial seeks to enroll 382 participants who will be block-randomized based on diagnosis into either the intervention or control group. The primary endpoint is the reduction of 90-day morbidity from 60 to 45% (Dindo–Clavien I–V). Secondary objectives include the 1-year overall survival, quality of life, length of hospital stay (including ICU, IMC, and general ward), readmission rates, compliance, and program adherence, product malfunction, vigilance reporting, improvement of the 6-min walking test by at least 20%, and hospital cost assessment.

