#### Secondary endpoints

Secondary endpoints of this study are the 1-year overall survival, the compliance and adherence to The Prehab App, the hospital cost effects of The Prehab App (readmission, length of hospital stay, reduction of cost), the quality of life, improvement of the 6-min walking test, the number of device failures, the vigilance of the device before surgery, and to identify patterns of repair, vascular remodeling, tumor microenvironment, and mitochondrial health in a future step.

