**Fig. 2 Fig2:**
[figure not shown]
Schematic layout of the app surface with exemplary risk scoring

The physician assesses the patient’s risk group using a desktop computer or the app. Then, the standalone software generates a personalized risk-based endurance exercise program and calculates the target heart rate (HR), incorporating maximum heart rate, resting pulse, and individual risk factors. Afterwards, the personalized training program is installed on the patients’ smartphones, where they will start with a 3–6-week aerobic interval training regimen (Fig. 1).

Prior to exercising, patients receive structured guidance as per the instruction manual and are screened for contraindications such as acute respiratory infections.

Before each session, patients complete a baseline QLQC-30 survey and a 6-min walking test. Each interval session lasts 47 min, including 5 min of warm-up and 5 min of cool-down, and will be performed 3 to 4 times. The training consists of alternating 2-min intense and 3-min less intense intervals. Heart rate and distance will be monitored during both the initial and final 6-min walking tests, as well as during individual training sessions. This monitoring will be facilitated via an Application Programming Interface (API) that interfaces with a smartwatch worn on either the right or left wrist tracking heart rate and distance.

Patients follow instructions on their wearable to stay within their threshold levels displayed on the screen, indicated by green (within) or red (outside) coloration. Vibration alerts signal training outside defined thresholds. Following the 6-MWT or exercise, patients are directed to a summary page to review data, and patient-reported outcome measures (PROMs) regarding symptoms experienced during exercise are collected. The Prehab program ends with a final 6-MWT and QLQC-30 survey. Then a second assessment calculating the risk scoring again by a physician follows directly before surgery. A second blood sampling takes place. The intervention results are then correlated with the 90-day follow-up data. The 90-day follow-up is undertaken as a telephone interview.

For the patient, no other equipment than a smartphone having The Prehab App installed and a smartwatch is needed. The app works with all common smartwatch and smartphone software on the market (e.g., iOS, Android).

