#### Assessments during the treatment phase

Intervention visits are performed weekly during the prehabilitation period and contain the evaluation of PROMs, compliance, safety audit, and retrieval of digitized data (V2–V7) (Table 1). Blood samples will be collected before the first and after the last interval training to further evaluate the safety of app-based exercise training. Additionally, the validity of the Karvonen method, including risk adjustments based on defined risk factors, will be assessed and correlated with the occurrence of clinical symptoms. To do so, 1–3 days before surgery, reassessment is conducted by performing a 6-min walking test and by evaluating patient history, risk factors, anemia, and heart rate (V5/V8).

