### Outcomes {12}

#### Descriptive measures, survival analyses, and cost analyses

Primary outcome: occurrence of any postoperative complication within 90 days after surgery according to the Clavien–Dindo classification (grades I–V).

Secondary outcomes: 1-year overall survival, 6-min walking distance, QLQ-C30 quality of life score, adherence and compliance, device failures, length of stay, days on ICU/IMC, readmission rates, hospital costs.

There will be an intention to treat analysis of all included patients fulfilling the in- and exclusion criteria. Data will undergo descriptive evaluation and assessment for normal distribution utilizing the Kolmogorov–Smirnov test with Lilliefors correction. Results will be presented as median or mean with standard deviation and interquartile ranges, and/or odds ratios with 95% confidence intervals, where applicable. Survival data will be computed as the time interval from the date of surgery to the date of death, or until censoring if patients are alive at their last visit/contact.

An intention-to-treat analysis will encompass all enrolled patients meeting the predetermined inclusion and exclusion criteria. Additionally, a per-protocol analysis will be conducted.

Compliance analysis in the intervention group includes the analysis of the number of exercises performed and the exercising within the predefined thresholds. We do expect a total of 191 6-MWTs delivering 65,000 pulse points and approximately 53 Mio. pulse points from 191 patients performing 10 exercises of 47 min each during the program that will define compliance as outlined in the following. Compliance of patients in the intervention group will be categorized according to the app algorithm (green: >75% of exercises performed and >75% of all measured values are green or yellow, yellow: 50–75% of exercises performed and 50–75% of all measured values are green or yellow, red: <50% of exercises performed and <50% of all measured values are green or yellow). Comparative compliance in the control group and the intervention group will be based on a descriptive comparison of the weekly safety calls in each group during the interventional phase as PROM analysis.

Surgical procedures and indications will be categorized based on OPS and ICD-10 codes. Subgroup analyses will be conducted using chi-square testing, *T*-testing, Kaplan–Meier survival analysis, and multivariate regression analysis.

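### The 6-minute walk endpoint has three different definitions, and the stated number of walk tests conflicts with the described schedule

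*Protocol article*

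**What the plan says.** The walk test appears as a secondary endpoint in three places:

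- Abstract, Methods: "improvement of the 6-min walking test by at least 20" per cent.
- Objectives {7}, Secondary endpoints: "improvement of the 6-min walking test, the number of device failures", with no threshold.
- Outcomes {12}: "Secondary outcomes: 1-year overall survival, 6-min walking distance, QLQ-C30 quality of life score". The same section says of results in general: "Results will be presented as median or mean with standard deviation and interquartile ranges".

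The number and timing of tests appear in four statements:

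- Intervention description {11a}: "Before each session, patients complete a baseline QLQC-30 survey and a 6-min walking test".
- The same paragraph: "Heart rate and distance will be monitored during both the initial and final 6-min walking tests".
- Assessments during the treatment phase, for the 1 to 3 days before surgery: "reassessment is conducted by performing a 6-min walking test".
- Outcomes {12}, in the paragraph on compliance in the intervention group: "We do expect a total of 191 6-MWTs delivering 65,000 pulse points".

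**The concern.** The three wordings lead to different analyses. The Abstract can be read as a patient-level responder rate or as a target for the group mean. The Secondary endpoints wording suggests a change score, and the Outcomes wording suggests a distance. Two analysts could report different results and each cite the protocol. Patients, researchers and surgeons are all unblinded, so there is good reason to settle the choice before data are seen.

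The responder reading is also the least efficient. It ignores the size of the change, and its meaning depends on the starting point: 20% is 50 m for a patient who walks 250 m and 100 m for one who walks 500 m (illustrative distances).

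The count is a second, separate problem. A single test per patient gives no change, so the expected total does not fit an endpoint worded as improvement.

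The walk test is the objective before-and-after measure of the fitness gain on which the trial's rationale rests. It would help to interpret either a positive or a neutral primary result.

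**Working it through.** **1. Test counts.** Inputs: 191 intervention patients and 10 exercises per patient (Outcomes {12}), with the timing statements set out above.

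| Reading | Arithmetic | Tests in the intervention arm |
|---|---|---|
| Expected count in Outcomes {12} | 191 × 1 | 191 |
| Initial and final | 191 × 2 | 382 |
| Initial, final and a separate test 1–3 days before surgery | 191 × 3 | 573 |
| Before each of 10 sessions | 191 × 10 | 1,910 or more |

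The final test and the preoperative reassessment may be one and the same. Even then the total is 382, twice the stated 191.

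The pulse-point figure can be checked against the count: 65,000 / 191 = 340 points per test. A 6-minute test lasts 360 s, so this is close to one reading per second (191 × 360 = 68,760). At that rate two tests per patient would give 382 × 360 = 137,520. The sampling rate is an assumption. The same sentence expects about 53 million points from the exercises, whereas one reading per second gives 191 × 10 × 47 × 60 = 5,386,200, a factor of 9.8. The two totals in that sentence therefore do not share one sampling rate. The count of 191 is explicit in any case.

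**2. What a responder cut would cost.** For a normal measure and a small effect, a binary cut keeps the fraction φ(z)² / [p(1 − p)] of the information. Here p is the share of patients reaching the cut, z the matching normal quantile and φ the normal density.

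- p = 0.50: φ = 0.3989, so 0.1592 / 0.25 = 0.64.
- p = 0.20: z = 0.842, φ = 0.280, so 0.0784 / 0.16 = 0.49.

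| Share reaching +20% | Information kept |
|---|---|
| 50% | 0.64 |
| 30% | 0.58 |
| 25% | 0.54 |
| 20% | 0.49 |
| 10% | 0.34 |
| 5% | 0.22 |

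The maximum is 0.64. The fraction falls below one half at a share of about 20% or less.

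**3. Illustrative power.** The plan's figure of 173 evaluable patients per arm reproduces. With 60% versus 45%, two-sided 0.05 and 80% power, n = [1.960 × √(2 × 0.525 × 0.475) + 0.842 × √(0.24 + 0.2475)]² / 0.15² = 172.8, rounded up to 173. I use it here only as a per-arm number. The means and SDs of percentage change below are assumptions; the article gives none.

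| Mean change, control vs intervention | SD | Responders | Power, responder test | Power, continuous |
|---|---|---|---|---|
| 0% vs 5% | 15 | 9.1% vs 15.9% | 48% | 87% |
| 5% vs 10% | 15 | 15.9% vs 25.2% | 58% | 87% |
| 2% vs 10% | 20 | 18.4% vs 30.9% | 77% | 96% |
| 0% vs 10% | 15 | 9.1% vs 25.2% | 98% | >99% |
| 10% vs 20% | 20 | 30.9% vs 50.0% | 96% | >99% |

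Over all scenarios tried (SD 10 to 20), the continuous analysis needed 0.18 to 0.62 of the sample size of the responder analysis. It was better throughout, but the practical gap runs from large to negligible depending on the assumed effect.

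**The case against.** The strongest reply is that no dichotomy is fixed. The 20% figure stands only in the Abstract. The Outcomes section names distance, gives summary statistics suited to a continuous measure, and the intervention description has distance recorded at the initial and final tests. A reader might infer from the Abstract that the trial discards most of the information in the walk test. The documents do not support that: no section makes the responder rate the only analysis, and more than half is lost only at a responder share of about 20% or less, which is not stated.

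A reader might also infer that only chi-square and t-tests are available for comparing the arms. That is not so. Statistical methods {20a} provides for multivariable regression adjusted for centre and baseline characteristics, surgical category as a covariate, and mixed-effects models. Detailed modelling of this endpoint may properly sit in the analysis plan, which is not shown, and its absence from the article is no error.

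The count of 191 is an expected data volume in a compliance paragraph. It causes no loss of information, and it does not show that a change cannot be computed, because initial and final tests are described elsewhere. Table 1 is not shown and may settle the visits in each arm. Nor does the point extend to the QLQ-C30, for which no threshold is set.

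All of this stands. What remains is that the published definitions disagree with one another and the count disagrees with the schedule. An unseen plan does not remove either contradiction from the article.

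**Conclusion.** The concern holds as an inconsistency in a secondary endpoint, with a separate error in the expected number of tests. Three sections define the walk endpoint in three ways. If the responder reading governed, at least about 36% of the information would be lost (1 − 0.64), and more than half if about 20% or fewer patients reached the cut. These fractions assume a normally distributed measure and a small effect. The power figures are illustrations on assumed inputs and say nothing about this trial's actual power for the endpoint, for which the article makes no claim.

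The count of 191 is half of what initial and final tests require in the intervention arm, and about a tenth of what a test before every session would require. The primary analysis and the primary sample size are untouched.

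**What to change.** Use one definition in the Abstract, the Secondary endpoints section and Outcomes {12}: preoperative 6-minute walking distance, analysed as continuous, with baseline distance, centre and surgical category as covariates. This lies within the regression framework of Statistical methods {20a}. Report the adjusted mean difference between arms with its 95% confidence interval, and keep the 20% responder rate as descriptive only.

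Reconcile the number and timing of tests across Intervention description {11a}, Assessments during the treatment phase and Outcomes {12}. Say whether the final test and the preoperative reassessment are the same test. Then correct the expected count and the pulse-point totals that follow from it.

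The cost is wording. The initial and final tests are already described, so no new data are needed, provided that Table 1 schedules both tests in the control arm as well.

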**Discussion:**

The LUMOS trial aims to evaluate the effectiveness of a digital prehabilitation program compared to an informational app only, prior to major surgery. The objective is to demonstrate the significant value of a digitized remote prehabilitation program in reducing perioperative morbidity, as well as addressing cost considerations.

**Trial registration:**

Trial registered in the European Database on Medical Devices (EUDAMED) (CIV-24-02-046162) and German Clinical Trial Registry (DRKS00033612, 13.05.2024), DMIDS-Number: 00015083, https://drks.de/search/en/trial/DRKS00033612. Goethe University Frankfurt: 024-1681-MDR/MPDG-zuständig multizentrisch, 06.05.2024.

**Supplementary Information:**

The online version contains supplementary material available at https://doi.org/10.1186/s13063-026-09977-w.

## Introduction

### Background and rationale {6a}

Surgery ranks among the top three causes of mortality in hospital settings [1]. Complications following surgical procedures impact up to 60% of patients, exerting both short- and long-term repercussions, including heightened morbidity, mortality, and prolonged hospitalization [2, 3]. These adverse events significantly influence patient satisfaction and overall experience. Notably, the risk of complications is influenced by various factors, including cancer diagnosis, age, frailty, and comorbidities that may be modifiable and optimized before surgery [4–7]. With nearly 40% of individuals in high-income countries aged over 65 years, and given that the average age of cancer and other condition diagnoses align, a considerable portion of patients with these conditions will necessitate surgical interventions in the coming years [8]. Evidence indicates that appropriate exercise interventions can notably enhance a patient’s physical fitness before surgery without exacerbating the risk of mortality from the underlying disease (3–6 weeks) [9–12]. Prehabilitation, a burgeoning field in medicine, focuses on improving individual patients’ physical fitness, therefore enabling them to adequately prepare for surgery. The preoperative period offers a critical window of opportunity wherein patients can enhance their overall physical condition, thus significantly impacting their outcomes. Person-centered prehabilitation of modifiable risk factors places the patient at the forefront of their perioperative journey. Recent randomized-controlled trials from Spain and the Netherlands have demonstrated the benefits of structured preoperative exercise programs, including reduced complications and accelerated recovery [13, 14]. For instance, a 4-week multimodal prehabilitation program significantly reduced severe complications in colorectal cancer patients compared to standard care. Frail patients undergoing elective major abdominal surgery particularly benefited from structured prehabilitation, experiencing improved aerobic capacity and reduced postoperative complications.

Our research group, in collaboration with the German Association for General and Visceral Surgery, conducted a scoping review to evaluate the potential and structured approach to prehabilitation [7]. We concluded that structured data assessment is essential for establishing comparability and enabling global implementation. Considering ongoing healthcare workforce shortages, lack of prehabilitation reimbursement, and the increasing availability of digital therapies, there is a compelling rationale for implementing remote, home-based, yet supervised and connected prehabilitation programs before major surgeries [15].

Our hypothesis is that patients undergoing structured prehabilitation with The Prehab App as a digitized individualized prehabilitation tool before major surgery will experience a reduction in the overall complication rate from 60 to 45%.

### Objectives {7}

#### Primary endpoints

The primary objective of this study is to analyze the safety and efficacy of The Prehab App before major surgical procedures. We hypothesize that the rate of postoperative morbidity can be reduced from 60 to 45%. The primary endpoint is the occurrence of any postoperative complication within 90 days after surgery according to the Clavien–Dindo classification (grades I–V).

#### Secondary endpoints

Secondary endpoints of this study are the 1-year overall survival, the compliance and adherence to The Prehab App, the hospital cost effects of The Prehab App (readmission, length of hospital stay, reduction of cost), the quality of life, improvement of the 6-min walking test, the number of device failures, the vigilance of the device before surgery, and to identify patterns of repair, vascular remodeling, tumor microenvironment, and mitochondrial health in a future step.

### Trial design {8}

The LUMOS trial is a prospective and randomized-controlled trial. Here, a 3-to-6-week interventional digital prehabilitation program (The Prehab App and medical guidance) with a digitized informational app (Ready4Op) will be compared against a control group receiving only the informational application as a parallel group. The patient allocation ratio is 1:1. The framework of the trial is superiority.

#### Study population

The study population will comprise 382 patients eligible for a major surgical procedure, possessing the mental, physical, and medical capacity to engage in a remote prehabilitation program. The program will last 3 weeks in cases where a cancer diagnosis does not necessitate neoadjuvant treatment or any other justified waiting period. For patients with a non-malignant diagnosis or those undergoing neoadjuvant therapy, the duration of the prehabilitation program will extend to 6 weeks. One hundred ninety-one patients will be randomized into the study arm using The Prehab App and 191 patients will be the controls using the Ready4Op App (Fig. 1).

**Fig. 1 Fig1:**
[figure not shown]
Study flow diagram of the LUMOS trial

## Methods: participants, interventions, and outcomes

### Study setting {9}

Patient recruitment is taking place at 6 trial centers in Germany; the hospitals vary between university hospitals and maximum care hospitals. All participating centers are highly experienced in major surgeries. The list of study sites can be obtained upon request from the corresponding author or under https://drks.de/search/de/trial/DRKS00033612. Reporting was done according to the SPIRIT guidelines (supplements 2) [16].

### Eligibility criteria {10}

The eligibility criteria for study centers are German hospitals that are experienced in major surgeries. The principal investigators and other investigators need to be doctors in surgery at the corresponding hospital.

#### Inclusion criteria

Patients must meet the following criteria to be eligible for the study:

The patient provides written informed consent, is able to understand the content of the study, understands the requirements for follow-up visits, and is willing to complete the questionnaires and provide the required information at follow-up visits.

The eligibility criteria encompass the following: (1) individuals aged ≥18 years, (2) participants possessing the cognitive capacity to comprehend the assigned task and provide written informed consent, (3) patients undergoing elective major surgeries including gastrointestinal resection, resection of the hepatobiliary and pancreatic system, endocrine glands, lung or bronchus, splenectomy, abdominal wall hernia repair, urological or gynecological resections, or vascular surgery devoid of cardiovascular procedures. The surgery can hereby be performed open, laparoscopic, or robotic assisted. Corresponding Operation and Procedure Classification System (OPS) codes are delineated in the supplemental material (Table S1).

Patients are only allowed to enter the trial if they provide their written informed consent and if the responsible investigator has verified that all selection criteria are met.

